### Data collection

Basic socio-demographic data such as religion, caste, occupation, education, and wealth quantile will be collected from both categories of clients. Additionally, mothers of the younger group will be interviewed for utilization of ANC, institutional delivery, postnatal care, full immunization, neonatal & child morbidity, treatment sought and any hospitalization for the child. Information will be collected on the number of ANC visits, tetanus toxoid immunization, iron–folic acid supplementation, and type of health facilities used for ANC and institutional delivery. Data on OOP expenditures incurred at public or private health facilities for ANC and institutional delivery will be elicited. The mothers will also be questioned about any illness during the neonatal period, its symptoms, treatment sought, type of health facility, and OOP expenditures incurred. Similarly, mothers will be asked about any episode of hospitalization for the child, place of hospitalization, and OOP expenditures incurred.

Mothers of children in the older child group will be asked about immunizations received by the child. Data collection based on the immunization card would be preferable; however, mothers’ recall will be used in cases where an immunization card is unavailable in the home at the time of the interview. The use the mother's recall for eliciting information on immunization received by the child is a standard practice in developing and developed countries and is used in several household surveys, for example, Coverage Evaluation Survey, District Level Health Survey, National Family Health Survey, and Demographic Health Survey (20). Second, the mother's recall in the absence of immunization card for collecting the information on immunization status has been validated in a variety of different settings (23, 24). The mother will also be questioned for any illness episode the child may have experienced during last 15 days and any hospitalization in the last 365 days. For the latter two events, information on the place where treatment was sought and the OOP expenditures incurred will be sought.

Additionally, mothers in both categories will be interviewed in the intervention and control area about the extent and quality of services offered by the ASHAs during the antenatal and postnatal home visits. Specific questions will be posed to mothers in the intervention area to assess the usage of the mobile application and their satisfaction with this mobile-assisted counseling.

### 
Data analysis

DID will be the primary analysis and will be based on the AHS and CEAHH data from intervention and control areas. Propensity scores will be used to match the women of intervention area with control area based on their socio-demographic characteristics. This will help to reduce the selection bias by taking into account the variation caused by known confounders. The AHS dataset for analysis comprises a total of 450 women: 225 from the intervention areas and 225 from the control areas. The CEAHH data have 1,053 women with a child aged 1–6 months each in intervention and control area. Similarly, a total of 1,391 women with a child aged 12–23 months in intervention and control area are part of the CEAHH dataset.

(a) PSM: The non-random choice of the two intervention blocks could result in selection bias. In order to minimize this bias, the PSM method will be used to control for demand-side characteristics that could influence utilization of various MNCH services. The PSM approach attempts to render the effects of different observed covariates X on participation as a single propensity score or index defined byP(X)=Pr(T=1∣X).The idea is to find, from a large group of control area women, those who are observationally similar to the intervention area women in terms of characteristics that are unaffected by the m-health intervention but that influence the utilization of key MNCH services (25). Then, each woman in the intervention arm will be matched with a woman in the control arm who is observationally similar (e.g. on socio-economic characteristics like literacy rate, caste, occupation of the mother, and age). The PSM estimator for the treatment effect on the treated can be specified as the mean difference of Y (i.e. institutional delivery or full immunization, or any other key indicator under consideration) over the usual support, weighting the comparison units by the propensity score distribution of eligible women in the respective categories. A typical cross-section estimator can be specified as follows:$$TOT_{PSM}=E_{P(x)|T=1}\{E[Y^{T}|T=1,P(X)]-E[Y^{C}|T=0,P(X)]\}.$$

(b) DID: This method essentially compares intervention and control groups in terms of outcome changes over time relative to the outcomes observed for a pre-intervention baseline. That is, given a two-period setting where *t*=0 before the program and *t*=1 after program implementation, letting $Y_{t}^{T}$ and $Y_{t}^{C}$ be the respective outcomes for a program beneficiary and non-treated units in time *t*, the DID method will estimate the average program impact as follows:$$DID=E(Y_{1}^{T}-Y_{0}^{T}|T_{1}=1)-E(Y_{1}^{C}-Y_{0}^{C}|T_{1}=0)$$In equation (1), *T*_1_=1 denotes treatment or the presence of the program at *t*=1, which is evaluated from CEAHH data, whereas *T*_1_=0 denotes absence of the program, which is evaluated using AHS data. Outcomes in the form of coverage of key MNCH services such as ANC, immunization and institutional deliveries will be assessed (25). Along with the above techniques, for each primary and secondary outcome, the estimated effect size and confidence intervals will be estimated to indicate the levels of precision.

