### Sample size

Two categories of individuals will be identified in each PSU: 1) women with one or more children aged 29 days to 6 months and 2) women with one or more children aged 12–23 months. The sample size for each category was estimated with respect to differences in coverage of two key MNCH services (institutional delivery and full immunization coverage) and neonatal and child morbidity rate for severe disease. For mothers with children in the younger age group, neonatal and child morbidity rates and institutional delivery coverage were used to determine sample size. For mothers with children in the older age group, the difference in rates of full immunization coverage was used to assess sample size.

We determined the sample size required to detect a 5% change in the coverage of MNCH services and neonatal and child morbidity rates, with a power of 80% and an alpha error of 5%. Baseline coverage of 15.1% and 30.8% for institutional delivery and full immunization coverage in control area, respectively, was assumed (18). Similarly, a neonatal morbidity rate of 18.9% for severe neonatal disease was assumed in the control area (4). With these parameters, sample sizes of 1,053 women with a child in the younger age group and 1,391 women with a child in the older age group from the intervention and control areas, respectively, were considered appropriate.

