#### Costing and cost-effectiveness assessment

First, costing will be undertaken from a societal perspective. Data on OOP expenditures for accessing MNCH services such as ANC, institutional delivery and curative care (including outpatient consultation and hospitalization) during the neonatal and infancy period will be collected during the CEAHH survey. A bottom-up costing method will be used to collect data on health system costs of implementing the m-health application as in the ReMiND project. This will comprise data on start-up costs such as planning meetings, development of software, and training of ASHAs. The initial start-up costs (such as trainings and software development) will be considered as capital costs and will be annualized based on the expected life of the product produced. Second, these will be apportioned to the two blocks of UP, assuming a scenario that the application can be scaled up in all of UP without further adaptation. Cost of implementation of the program will be assessed in terms of resources of implementing partners such as CRS and Vatsalya, which implemented the program in the intervention area. These resources include staff salaries, equipment, building and space, drugs and consumables, and other overheads. Health system costs for delivering services through ASHAs will be assessed by collecting data on performance-based incentives paid to the ASHAs. For the purpose of cost scale-up analysis, only those start-up costs will be considered that are likely to be incurred by the health system as part of scale-up – for example, adaptation of the software in the new state, trainings, and any manuals to be developed.

Other health system costs that are incurred for delivery of preventive and curative MNCH services will be drawn from published studies (26–28). Together with data on health service utilization and OOP expenditures (as obtained from the CEAHH survey), epidemiological parameters (as obtained from a review of literature) and data on health system costs collected from the present study, overall cost of delivering MNCH health services will be estimated. This will also be used to generate the estimate for standardized cost of delivering MNCH services (preventive and curative) at the district level, with and without the m-health application.

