**Fig. 4 F0004:**
[figure not shown]
Decision model for cost-effectiveness (maternal health) study of m-health application for ASHA workers as part of ReMind project.

Costs and benefits will be analyzed from both a health system and a societal perspective. Benefits on health status will be measured in terms of illness episodes averted, child deaths prevented, maternal deaths prevented, life years gained and DALYs averted. Evaluation of health benefits will be undertaken by modeling the improvements in service utilization and reduction in illnesses during the neonatal period and infancy, as well as reduction in maternal and infant mortality and disability. Finally, reduction in DALY as a result of implementation of the m-health application will be estimated. The effects on maternal and infant mortality will be modeled for the following intermediate consequences: improvement in ANC and institutional delivery; reduction in neonatal and infant morbidity, predominantly pneumonia and diarrhea; and improvements in care seeking for sick newborns. The existing evidence based on the LiST model and pertaining to investigation of improvements in MNCH-related preventive services will be reviewed to assess these relationships. This will build on the existing evidence that is used for modeling the effect of improvements in these preventive services, as well as care seeking in the LiST (Lives Saved Tool) model (30). Benefit will also be measured in terms of improvement in service coverage. A composite service indicator will be developed to assess the change in service coverage.

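### The societal costing has no described source for what households spend on a home delivery, because delivery spending is elicited only for facility births

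*Protocol article*

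**What the plan says.** In the protocol article, the Data collection section describes the interview for mothers of younger children: "Data on OOP expenditures incurred at public or private health facilities for ANC and institutional delivery will be elicited". Delivery spending is limited twice, by place (a public or private facility) and by event (institutional delivery).

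The section on costing and cost-effectiveness assessment says that "costing will be undertaken from a societal perspective". It lists the household items again as "Data on OOP expenditures for accessing MNCH services such as ANC, institutional delivery and curative care", and it names the household survey as the source when the cost inputs are assembled: "Together with data on health service utilization and OOP expenditures (as obtained from the CEAHH survey". Published sources have a different role: "Other health system costs that are incurred for delivery of preventive and curative MNCH services will be drawn from published studies". A literature review is also named, but for epidemiological parameters. The text after Fig. 4 adds a second viewpoint: "Costs and benefits will be analyzed from both a health system and a societal perspective".

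The Theory of change section treats home delivery as something that demand generation can alter. It reports that 28% of women in the state who deliver at home saw no need for a facility birth. The Sample size section gives the planning value: "Baseline coverage of 15.1% and 30.8% for institutional delivery and full immunization coverage in control area".

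**The concern.** From a societal viewpoint, the household cost of moving one birth from home to a facility is what the family pays at the facility minus what it would have paid at home, for example for an attendant, medicines or supplies. The described survey measures the first term. No section describes how the second is obtained, whether from the survey or from the literature.

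The decision model credits health gains to better uptake of facility delivery. If the spending avoided at home is missing, the same shift is charged with facility spending and no offset. The household delivery component of the incremental cost would then be biased against the intervention. The survey is the only post-intervention round described, so an item that is not asked cannot be recovered from these mothers later.

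**Working it through.** **Inputs**

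- Baseline facility delivery in the control area: 15.1% (Sample size).
- Planned detectable change: 5%, with 80% power and 5% alpha (Sample size).
- Household spending on a facility birth (F) and on a home birth (H): neither is given. H is written as r × F, with r assumed between 0 and 1 and F set to 1 unit.

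**Reading of the 5% change.** The article gives no cost figure to reproduce, but its sample sizes show what 5% means. With a pooled two-proportion formula, two-sided and without continuity correction:

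- 18.9% vs 23.9% gives 1,055 per area (stated 1,053).
- 30.8% vs 35.8% gives 1,394 per area (stated 1,391).
- 15.1% vs 20.1% gives 910, so morbidity sets the younger-group size.

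The change is therefore 5 percentage points, and dp = 0.05.

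**Household delivery cost**

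1. With facility proportion p, mean household cost per delivery is p × F + (1 − p) × H.
2. Moving from p0 to p1 = p0 + dp changes this by dp × (F − H).
3. If H is omitted, the change becomes dp × F.
4. The overstatement is dp × F − dp × (F − H) = dp × H, which is 0.05 × H per delivery.

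Example with r = 0.5: (0.201 + 0.799 × 0.5) − (0.151 + 0.849 × 0.5) = 0.6005 − 0.5755 = 0.025. With H omitted it is 0.201 − 0.151 = 0.050.

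Incremental household delivery cost per 1,000 deliveries, in units of F:

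| Assumed r = H/F | H counted | H omitted | Overstatement | Ratio |
|---|---|---|---|---|
| 0 | 50.0 | 50 | 0 | 1.00 |
| 0.10 | 45.0 | 50 | 5.0 | 1.11 |
| 0.25 | 37.5 | 50 | 12.5 | 1.33 |
| 0.50 | 25.0 | 50 | 25.0 | 2.00 |
| 0.75 | 12.5 | 50 | 37.5 | 4.00 |
| 1.00 | 0 | 50 | 50.0 | not defined |

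The baseline level p0 cancels, so only dp and H matter. The bias is zero if H = 0 or dp = 0, and it changes sign if facility delivery falls.

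**The case against.** The strongest reply is that the article condenses instruments and a model that are not shown. Two structured interview schedules exist, the decision-model figures are not available here, and the list of household items in the costing section is introduced as examples. A home-birth item or a home-branch cost could exist without being mentioned.

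This stands against one inference a reader might draw, that home delivery is costed at zero. No section assigns it zero or any other value. It does not remove the gap. The open-ended list does not undo the double restriction in Data collection, and no other source of household spending is named.

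Three further inferences also fail:

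- A reader might take the complement of the planning value, 100 − 15.1 = 84.9%, as the size of the problem. It is a baseline assumption, not a 2015 survey result, and it does not enter dp × H.
- A reader might say that the expected fall in out-of-pocket spending cannot be tested for delivery. The Theory of change section ties that fall to public versus private care seeking, which facility spending data can address. What remains unmeasured is the net household effect of moving from home to facility.
- A reader might apply the ratios in the table to the whole incremental cost. They concern one component only. Start-up, implementation, ASHA incentive, health system and other household costs also enter the total.

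It is also fair that the schedules are described as already developed, so adding an item may mean reopening them.

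**Conclusion.** The concern holds in a limited form. As described, the societal analysis has no source for household spending on a home delivery, which is the state the intervention is meant to reduce. If that spending is left out, incremental household delivery cost is too high by dp × H per delivery, or 0.05 × H at the planned change. This rests on H being above zero and facility delivery rising. Any percentage depends on an assumed H/F, because the document gives neither amount.

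The coverage objective and the health system perspective are untouched. The share of total incremental cost or of cost per DALY averted cannot be derived, so the document does not support a statement that the cost-effectiveness ratio is materially wrong. This is an inexpensive improvement to one part of a secondary objective.

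**What to change.** In the younger-group schedule, ask every mother in both areas about delivery-related out-of-pocket spending, whatever the place of birth. Use the home-birth mean as the household cost of the home-delivery branch in the societal model, and say so in the costing section.

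If the schedule can no longer be changed, name an external source for H and vary the value in sensitivity analysis, with zero included in the range.

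The first option needs one short block of questions to mothers who are already being interviewed and no extra sample. Its downside is a slightly longer interview. The second needs no fieldwork, but it relies on a value from outside the study area or period.

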To supplement community health worker training and retention of knowledge, mobile technology has been considered an effective and sustainable method in developing countries (7). With the widespread use of mobile phones in the rural areas of India, reliable health information can easily be made accessible even to the remotest areas (8). Thus, built-in tools with health messages in the mobile phones can be used by the community health workers as an aid for counseling pregnant women and nursing mothers. A study conducted in rural areas of Tamil Nadu in India to assess the feasibility of text messaging in delivering maternal and child health care showed that mobile health messages were well perceived and accepted in the community (9). Knowledge about the recommended minimum number of ANC visits was reported to increase from 10 to 37% after women received text messages for health promotion on mobile phones (9).

Use of technology in the health sector, especially in rural areas that have significant health workforce deficiencies, has been endorsed by the government of India at the highest level (10). In this context, the ReMiND (Reducing Maternal and Neonatal Deaths) project was introduced in two blocks of the Kaushambi district in UP. As part of this project, a mobile health (m-health) application that runs on open source CommCare software has been introduced as a job aid for ASHAs. This m-health platform tracks and supports clients for the ASHAs and provides individualized service and counseling. It replaces paper registers and flip charts with open source software that runs on inexpensive phones. During home visits, it aids ASHAs to register clients and provides real-time guidance through key counseling points, decision support, and simple referral algorithms.

Similar m-health interventions in other countries have proven beneficial. For example, in Afghanistan m-health resulted in 20% improvement in antenatal attendance and a 22.3% improvement in the number of women receiving skilled deliveries at a health facility (11). In terms of quality of counseling (i.e. whether a client receives complete and accurate information), a study in India showed that after a period of 4 months of use of the CommCare application, frontline workers had increased their knowledge retention of at least three danger signs across all key health categories, from 48% at baseline to 70% (12).

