## Background

### Study setting

The study will be conducted in the Kaushambi district in UP. Out of the district's eight community development blocks, the m-health intervention has been implemented in two blocks: Mooratganj and Manjhanpur.

The Catholic Relief Services (CRS) with the help of a local NGO, Vatsalya, introduced the CommCare m-health application to 259 ASHAs in the two intervention blocks in 2012. The ASHAs in the ReMiND project were provided with basic Java-based mobile phones operating on open source CommCare software (15). Extensive trainings of ASHAs were done in both blocks on the use of these phones. The ReMiND application has tailored content and guides the ASHA through the course of a woman's pregnancy and newborn child care. ASHAs use the application for the following purposes:To register each pregnant womanTo update her ANC record during home visits on the mobile applicationTo track her from pregnancy into the postpartum periodTo track the health of the newbornTo track the status of routine immunization until 2 years of ageTo provide appropriate counseling and support at each of these stepsThe phones contain locally relevant audio and visual prompts to help ASHAs navigate through the application. These recordings and pictures enrich the counseling experience of ASHAs during their home visits. The application uses the data entered about the pregnancy to guide ASHAs in providing timely and appropriate health information; it helps them to prioritize home visits; and it employs algorithms to assist in the early identification, treatment, and rapid referral to appropriate care of any danger signs among pregnant women or neonates (Fig. 1). While ASHAs have many tasks assigned to them, the key one is to identify pregnant women and visit them throughout the course of their pregnancy, seeing them through delivery in a safe facility and appropriate newborn care.

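### Neonatal morbidity and care-seeking differences enter the DALY model at face value, although the intervention may itself change what mothers recognise and report

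*Protocol article*

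**What the plan says.** **Measurement.** For the younger group, the Data collection section states: "The mothers will also be questioned about any illness during the neonatal period, its symptoms, treatment sought". Hospitalisation of the child is asked separately. The section defends mothers' recall for immunisation only. It describes no clinical confirmation of neonatal illness.

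**Role in sizing.** The Sample size section says "neonatal and child morbidity rates and institutional delivery coverage were used to determine sample size", and that "a neonatal morbidity rate of 18.9% for severe neonatal disease was assumed in the control area".

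**What the intervention does.** Study setting says of the application that "it employs algorithms to assist in the early identification, treatment, and rapid referral to appropriate care of any danger signs", and names neonates as well as pregnant women. Theory of change runs through better counselling and knowledge, and expects better care seeking during illness.

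**Use in the economic model.** Under Costing and cost-effectiveness assessment, the intermediate consequences that drive modelled mortality include "reduction in neonatal and infant morbidity, predominantly pneumonia and diarrhea; and improvements in care seeking for sick newborns". The third limitation in the Discussion adds that whatever differences arise in neonatal care seeking, postnatal care and the like will be modelled as DALYs averted.

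**Analysis.** Matching uses socio-demographic characteristics, followed by DID. The Discussion accepts that neither participants nor outcome assessors can be blinded. It does not mention differential recognition of illness.

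**The concern.** A reported illness is the product of two things: the newborn was ill, and the mother recognised and reported it. The intervention is designed to reduce the first and may raise the second.

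DID removes reporting error that is constant within an area or common to both areas. It cannot remove a change that occurs only in the intervention area after the start, because that is exactly the contrast it estimates. Matching on caste, education, occupation or age does not touch it either.

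A real reduction in morbidity could therefore be attenuated, or a null effect could look like an increase. Care seeking expressed per reported-ill newborn would have a denominator that moves with recognition. Since the protocol turns these differences into health gains without a check, the artefact would pass into deaths averted and the cost per DALY.

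**Working it through.** **Inputs from the protocol.** Control morbidity 18.9%; 5-point change; 80% power; 5% alpha; 1,053 women per area in the 2015 survey; 225 per area in the 2011 baseline (Data analysis).

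**Assumed.** A reporting ratio r, the factor by which recognition and reporting rise in the intervention area in 2015 and nowhere else. The protocol gives no value for mothers.

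**1. The plan's own figure.** n = (1.960 + 0.842)² × [p₁(1−p₁) + p₂(1−p₂)] / d².
- Morbidity 18.9% vs 23.9%: 1,052.2, so 1,053 per area. This reproduces the stated number.
- Institutional delivery 15.1% vs 20.1%: 907. Morbidity is therefore the binding input for the younger group.
- A fall, 18.9% to 13.9%, would need 857. The stated number matches a rise, which makes the sample larger than a fall requires; it is no shortfall.

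**2. Attenuation of a true fall from 18.9% to 13.9%.** Measured difference = 13.9 × r − 18.9, in points.

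| r | Measured difference |
|---|---|
| 1.00 | −5.0 |
| 1.05 | −4.3 |
| 1.10 | −3.6 |
| 1.20 | −2.2 |
| 1.36 (18.9/13.9) | 0.0 |

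The sign reverses only above 1.36.

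**3. False rejection with no true effect, planned DID.** Three cells at 18.9%, and the intervention area in 2015 at 18.9% × r. Simple binomial variances, no clustering, two-sided 5% test.

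Variance = 2 × 0.189 × 0.811/225 + 0.189 × 0.811/1,053 + q(1−q)/1,053, with q = 0.189r.
- r = 1.10: q = 0.2079, SE = 0.0408, shift 0.0189, z = 0.46. Rejection 7.5%, of which 6.7% towards an increase.
- r = 1.20: q = 0.2268, SE = 0.0409, shift 0.0378, z = 0.92. Rejection 15%, nearly all towards an increase.

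The two baseline cells contribute 0.00136 of a total variance of about 0.00167, so the DID is imprecise. This keeps the false-rejection rate moderate, but the bias in the point estimate (+1.9 and +3.8 points) is unchanged, and the point estimate is what a decision model uses.

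**4. Care seeking per reported-ill newborn (illustration, all rates assumed).** Of 100 cases recognised before, 60 are taken to care; recognition adds 20 cases.
- If 30% of the added cases are taken to care: (60 + 6)/120 = 55%, down from 60%.
- If 80% are: (60 + 16)/120 = 63.3%, up from 60%.

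In both cases more children receive care (66 or 76 instead of 60, from the same number surveyed). The ratio can move either way with no change in illness.

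**The case against.** **Raised recognition among mothers is inferred.** The algorithms assist ASHAs. The only figure on danger signs, in the Introduction, concerns workers in a cited study: "frontline workers had increased their knowledge retention of at least three danger signs across all key health categories, from 48% at baseline to 70" percent. A reader might take 70/48 = 1.46 as a plausible reporting ratio. The protocol does not support that: it is a ratio of shares of workers knowing at least three signs, not of illness reports by mothers. The Discussion also describes the application as limited to antenatal care, delivery and immunisation, with neonatal effects as spin-offs. This sits badly with Study setting, but it does weaken the presumption. This part of the objection stands, so the size of the bias is an assumption.

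**The interview schedules are not shown.** A reader might infer from the word "its" that symptoms are asked only after an illness is reported, so that unrecognised signs are never recorded. One summarising sentence cannot carry that. The schedules were built from existing national survey tools and may already prompt for signs. This stands.

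**The false-alarm risk looks larger in a 2015-only comparison.** With 1,053 per area that test would reject about 19% of the time at r = 1.10 and 57% at 1.20. It is not the primary analysis; the DID figures above apply.

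**Newly recognised illness may be mild** and fail a severe-disease definition, so multiplying the severe rate by the full r may overstate the shift. This also stands, and is a reason for a stated symptom rule.

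**The primary objective is service coverage.** Antenatal care, institutional delivery and immunisation are not affected by this point.

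None of this shows that the planned analysis could detect or remove a recognition shift, or that taking the differences at face value in the DALY model is safe.

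**Conclusion.** The point holds as a risk to the morbidity and care-seeking inputs of the cost-effectiveness analysis. The outcome rests on the mother's report, the intervention has a plausible route to that report, neither DID nor matching can separate recognition from illness, and the protocol converts the differences into DALYs without a check.

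If reporting rises by 10% to 20% in the intervention area only, a true 5-point fall is measured as 3.6 to 2.2 points. With no true effect, the DID rejects about 7.5% to 15% of the time. These figures assume an unchanged control area, no clustering, and a reporting gain that applies fully to severe disease.

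A reader might infer that the morbidity effect is certain to be biased towards harm, or that its sign will reverse. The protocol supports neither. No reporting ratio for mothers is given, and reversal of the planned effect needs one above 1.36. For care seeking among reported-ill newborns, even the direction is open. The primary coverage results stand apart from this issue.

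**What to change.** 1. Report treatment seeking and hospitalisation per surveyed child (a child who survived to at least 29 days, given the sampling frame) alongside any figure per reported-ill newborn. The per-child rate also moves with true illness, so the two should be read together.
2. Replace the rule in the third limitation. Show the DALY result with and without the mother-reported morbidity difference, and add a sensitivity range for the intervention-area reporting ratio, for example 1.0 to 1.4, labelled as an assumption.
3. Classify severe neonatal disease from reported symptoms by one rule in all four blocks. Keep items that match the AHS unchanged. Ask symptom items of every mother only if this does not break comparability with the 2011 AHS; if the schedule already does so, say so.
4. List differential recognition among the limitations.

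Items 1, 2 and 4 use data already planned and need no extra participants. The cost is some additional analysis and a wider reported range for the cost per DALY. Some differential recall will remain whatever is done.
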